**3. STUDY DESIGN**

In this section we address the design of the study, the details of (a) the 'BOFT+' intervention and (b) The 'Healthy toddler' intervention (i.e. the theoretical framework and content), the outcome measures of the study, the procedure of the study (including inclusion of participating centers, randomization procedure, training of the participating Youth Health Care-teams (YHC-teams), inclusion of parents/families in the study), power considerations regarding the differences in outcomes between each Intervention group and the Control group that can be detected in this study, the proposed statistical analyses of the results, and the time schedule for the study.

In this study we will evaluate (a) the 'BOFT+' intervention with - as primary starting point - a focus on child rearing issues that are relevant for the development of behaviors related to overweight, starting at birth, increasing self esteem of parents, anticipating on parenting by reinforcing all positive parenting strategies from early age on, using the relatively simple elements of motivational interviewing (empathy and no use of warnings, confrontations, discussion), using elements of mediation therapy and using elements of learning theory, stimulus control, modeling and operant conditioning (based on ZonMw project # 50-50140-98); and (b) The 'Healthy toddler' intervention with - as primary starting point - a focus on behaviors related to overweight using E-health in combination with face-to-face counseling and motivational interviewing for parents of young toddlers (18-24 months) (based on ZonMw project # 4010.0033). The 'Healthy toddler E-health module provides tailored advice to parents regarding healthy behaviors of their toddler and related child rearing practices; the face-to-face counseling addresses issues raised by the E-health module, including questions that the parents may have, using motivational interviewing techniques as proposed by the YHC-Overweight-prevention-protocol (Hirasing et al, 2005).

(a) 'BOFT+' intervention

The 'BOFT+' intervention has - as primary starting point - a focus on child rearing issues that are relevant for the development of behaviors related to overweight. By doing so it aims at implementing healthy life-style habits continuously, from early age on (from birth on) during guidance offered to parents by YHC in the whole preschool period. An authoritative parenting style means high levels of effective parenting, not many inter-parental conflicts en high parental self-efficacy. A healthy lifestyle can be reached by healthy eating, physical activity and the use of positive parenting. In the current study the effect of the intervention up to (and including) age 24 months old will be evaluated with a final follow-up measure at age 36 months.

The strategy of the 'BOFT+' intervention is based on results of a previous study on determinants of behavior that is related to overweight in young children (Boere-Boonekamp 2005; ZonMw Grant # 50-50140-98). In this intervention the education and counseling will not only focus on eating habits and exercise, but also on childrearing issues, by using elements of the learning theory and enlarging parental sensitivity together with high expectations concerning the possibility of self-control of the child (the so called authoritative parenting style. YHC nurses will apply the new approach during each YHC-contact with parent(s) in the preschool period. Examples of the techniques that will be used are: modeling, stimulus control, operant conditioning such as intermittent confirmation.

(b) The 'Healthy toddler' intervention

The 'Healthy toddler' intervention has - as primary starting point - a direct focus on four behaviors related to overweight as defined in the YHC-Overweight-prevention-protocol that start to be of relevance in young toddlers: daily exercise/outdoor playing, family breakfast daily, few sugar sweetened drinks, minimal TV time (so-called 'BOFT' behaviors). Child rearing issues related to these behaviors are addressed as well in the 'Healthy toddler' intervention.

The 'Healthy toddler' intervention consists of an E-health module with tailored advice to parents regarding the 'BOFT' behaviors of their toddler and related child rearing practices, which is combined with face-to-face counseling in the setting of regular YHC at the child age of circa 18 months for the first time and at child age of circa 24 months for the second time. The E-health module is offered prior to both visits, and is repeated, as a reminder, a month after both visits. The face-to-face counseling will address specific issues raised by the E-health module, including questions that the parents may have. As proposed by the YHC-Overweight-prevention-protocol YHC-professionals will make use of motivational interviewing techniques in the two counseling sessions. As specific YHC-visiting schemes vary by region in the Netherlands, some variation will be allowed regarding age of application.

The study is designed as a cluster-randomized trial (c-RCT) with two intervention conditions (see above) and a control condition ('usual care'), with inclusion shortly after child birth, repeated measurements prior to and during the interventions, and a follow-up measurement at age 36 months, which is circa 12 months after the last intervention contact with the parents around the age of 24 months old in both intervention groups. The YHC-team (Consultatiebureau-team) is the unit of randomization in order to avoid contamination between the intervention condition and the control group condition within teams (Campbell et al., 2004).

Circa ten regional services providing Youth Health Care for preschool children (in Dutch: Jeugdgezondheidszorg 0-4 jaar, or Ouder- en Kindzorg) from metropolitan and non-metropolitan areas, to be selected in an open procedure, will participate in the study with a total of 45 Youth Health Care teams (Consultatiebureau-teams). Within each service, YHC-teams will randomly be assigned to either one of the two intervention groups or the control group. The last follow-up measurement in the study that we propose now will take place at the age of circa 36 months, during a regular visit to the YHC center in combination with a self-report questionnaire. A process and cost-effectiveness evaluation will accompany the effect evaluation. When the study is successful, follow-up projects with continuation of the interventions and/or follow-up measurements at older age will be proposed at ZonMw or other funding organizations in the future.

Figure 1.

***Flowchart of the study***[figure not shown]

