## SUMMARY

This study aims to evaluate the effects on the prevention of overweight of three approaches that are currently being applied in Dutch preventive Youth Health Care (YHC) to parents of infants and toddlers: (a) 'Usual care', i.e. common advices regarding nutrition and playing of the infant and toddler; (b) 'BOFT+', i.e. a training of YHC-nurses regarding their skills to advice parents regarding parenting; and (c) the 'Healthy toddler', i.e. a specific advice to parents of toddlers at age 18 months and 24 months regarding nutritional habits, playing habits and watching TV, supported by a written advice generated by Internet.

Forty-five Youth Health Care (YHC) teams of circa 10 regional YHC providers will participate in this study with net 1.500 children. The 45 teams will be assigned at random to (a) continue 'Usual care' (15 teams), or (b) to participate in the training for nurses regarding parenting skills (i.e. 15 'BOFT+' teams), or to (c) YHC-teams that will apply the 'Healthy toddler' face-to-face consultation at age 18-months regarding nutritional habits, playing habits and watching TV, supported by an Internet generated, tailored written advice (15 teams). Informed consent to participate in this study will be obtained from the parents during a regular home visit by member of the YHC-team circa 2 weeks after birth; follow-up of the parents and their children is till the child is 36 months old.

According to the current YHC Overweight prevention protocol ('Overbruggingsplan') YHC-teams, in order to contribute to the prevention of overweight in childhood should promote 1) breastfeeding, 2) outdoor exercise, activity and play, 3) having breakfast daily, 4) few soft drinks and 5) less TV time (in Dutch: 'B-BOFT'-behaviors).

(a)

'Care as usual' consists of common advices regarding nutrition and playing of the infant and toddler, and the above-mentioned 'B-BOFT' behaviors are part of such advices that are given according to the Product Description YHC, i.e. the regular scheme of YHC visits, e.g. through oral information and generic information leaflets.

(b)

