**POWER CONSIDERATIONS AND DETECTABLE DIFFERENCES**

We expect to receive complete data of 1.050 parents/toddlers at follow up at age 36 months old, equally divided over the 2 intervention groups and the control group. We assume equal standard deviations in the intervention groups and the control group, alpha of 0.05 and power of 0.80. We applied a correction factor to account for the cluster design, assuming an average cluster size of 23,3 toddlers (1.050/45) and an intra-class correlation coefficient of 0.10. For this expected sample size and assumptions, we calculated minimal detectable differences between an intervention and the control group at follow-up. We applied standard deviations and proportions/percentages reported in the literature or currently available data from the prior ZonMw projects (# 50-50140-98; # 4010.0033).

Target behaviors at age 36 months old:

Regarding the mean number of the reported minutes of physical activities of the children per day at age 36 months old, the study can detect a difference between intervention/control group of 18 minutes/day (SD=52 min/day). Regarding the mean consumption of sugar-sweetened drinks in glasses per day, a difference of 0.5 glasses/day (SD=1.5 glasses/day) can be detected. Regarding the mean number of minutes of TV viewing per day, a difference of 11 minutes/day can be detected (SD=32 minutes/day).

BMI at age 36 months old:

A difference of 0.44 BMI points between the mean BMI in the intervention group and the mean BMI in the control group at age 36 months can be detected by the study (SD=1.3) (Atkin & Davies, 2000).

Since we will use repeated measures (at age 15 months respectively 24 months in addition to 36 months) as covariates in the analyses, the power will be higher than indicated, which will facilitate the exploration of interaction effects of child gender, social disadvantage, ethnic background, and parental overweight status.

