## 7. STATISTICAL ANALYSIS

### **Intervention effect:**

To assess the intervention effect, multilevel analyses will be applied to allow for dependency between the individual measurements within the randomized YHC-teams (Campbell et al., 2004). The multilevel approach is also appropriate for the analyses regarding longitudinal data in the study. Multilevel linear regression analyses will be conducted for the continuous outcome variables with group (intervention or control) as independent variable and baseline values and potential confounders as covariates. Multilevel logistic regression will be performed in case of dichotomous outcome variables.

Additionally, effect modification by gender, parental educational level, ethnicity, and parental overweight status will be conducted by introducing an interaction term into the regression analyses. If this interaction term reaches statistical significance, stratified analyses will be carried out.

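### Teams are randomised within regional services, but the stated multilevel model names only the team level; if services differ materially, standard errors are too wide and tests conservative

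*Protocol*

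**What the plan says.** Section 3 (Study Design) describes the allocation. "The YHC-team (Consultatiebureau-team) is the unit of randomization", and the teams come from several organisations: "Circa ten regional services providing Youth Health Care for preschool children", drawn from both metropolitan and non-metropolitan areas. The allocation is then described as: "Within each service, YHC-teams will randomly be assigned to either one of the two intervention groups or the control group". Service is thus a stratification factor. The Summary gives the numbers: "Forty-five Youth Health Care (YHC) teams of circa 10 regional YHC providers will participate in this study with net 1.500 children", with 15 teams per arm.

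Section 7 (Statistical Analysis, Intervention effect) describes the model: "multilevel analyses will be applied to allow for dependency between the individual measurements within the randomized YHC-teams". Its terms are set "with group (intervention or control) as independent variable and baseline values and potential confounders as covariates". Service appears neither as a level nor as a covariate. The confounders are not listed, and nothing in the text excludes service.

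The power section (section 4) uses one intra-class correlation of 0.10 at team level, with no service component.

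**The concern.** When units are randomised within strata, the stratum's contribution largely cancels from the comparison of arms. A model without the stratum leaves that contribution in the between-team variance, and so reports a larger standard error than the design delivers. Confidence intervals are then too wide and the test rejects less often than its nominal 5%.

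The protocol gives reasons to expect services to differ. They span urban and non-urban areas, visiting schemes vary by region (sections 3 and 5), and the introduction links the rise in overweight to social disadvantage and ethnicity. It gives no variance figure. With an effective sample of about 108 per arm after the cluster correction, unused precision is worth having. If service is added only after outcomes are known, the choice could look driven by the results.

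**Working it through.** **Inputs from the protocol.** 45 teams, 15 per arm. "We expect to receive complete data of 1.050 parents/toddlers at follow up at age 36 months old, equally divided", so 350 per arm and 1,050/45 = 23.33 per team. ICC 0.10. "alpha of 0.05 and power of 0.80", with sidedness not stated.

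**Assumed input.** The share f of the between-team variance (0.10 on a total variance of 1) that lies between services. The protocol gives none, so f = 0, 0.10, 0.25 and 0.50 are shown.

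**Step 1: the plan's own figures.** Design effect = 1 + (23.33 − 1) × 0.10 = 3.233. Effective n = 350/3.233 = 108.2 per arm. Detectable difference = (z_alpha + z_power) × √(2/108.2) SD.
- One-sided 0.05: 0.338 SD, giving 17.6 min activity, 0.507 glasses, 10.8 min TV and 0.439 BMI points. The protocol states 18, 0.5, 11 and 0.44.
- Two-sided 0.05: 0.381 SD, giving 19.8, 0.57, 12.2 and 0.495.

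The stated figures thus reproduce on a one-sided basis. That is a separate matter; they do not depend on how service is handled.

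**Step 2: idealised gain, arms exactly balanced within services.** Variance of the difference with service in the model = 2 × [0.10(1 − f)/15 + 0.90/350].
- f = 0: 2 × (0.006667 + 0.002571) = 0.01848, SE 0.1359 SD.
- f = 0.25: 2 × (0.005 + 0.002571) = 0.01514, SE 0.1231 (ratio to f = 0: 0.91).
- f = 0.50: 2 × (0.003333 + 0.002571) = 0.01181, SE 0.1087 (ratio 0.80).

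The two-sided detectable difference is 0.381, 0.345 and 0.304 SD. For BMI (SD 1.3) that is 0.50, 0.45 and 0.40; on the one-sided basis it is 0.44, 0.40 and 0.35. These are best-case figures, because they presume exact balance and charge nothing for the service terms.

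**Step 3: simulation with uneven strata.** Team means were simulated for ten services, five with 4 teams and five with 5. Each arm was present in every service and had 15 teams overall. There were 6,000 runs per scenario. The means were analysed with arm only (45 − 3 = 42 df) and with arm plus service as fixed effects (45 − 3 − 9 = 33 df), two-sided 5%. Entries are team-only / with service.

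| f | Mean reported SE | Actual SD of estimate | Type I error | Power at 0.38 SD |
|---|---|---|---|---|
| 0 | 0.1350 / 0.1385 | 0.1359 / 0.1397 | 5.0% / 4.9% | 78% / 75% |
| 0.10 | 0.1346 / 0.1330 | 0.1317 / 0.1348 | 4.4% / 4.8% | 79% / 79% |
| 0.25 | 0.1340 / 0.1250 | 0.1269 / 0.1267 | 4.0% / 5.4% | 81% / 84% |
| 0.50 | 0.1332 / 0.1104 | 0.1160 / 0.1134 | 2.4% / 5.1% | 82% / 91% |

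Monte Carlo error is about √(0.05 × 0.95/6,000) = 0.3 points on a 5% rate, so the 5.4% is compatible with 5%.

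The team-only SE overstates the actual spread by about 6% at f = 0.25 (0.1340/0.1269) and 15% at f = 0.50 (0.1332/0.1160). At f = 0.25 the estimate itself is equally precise under both models; only the reported SE and the test differ.

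**The case against.** The strongest reply is that the text does not settle the matter. The confounder list is open, the model is not limited to two levels, and a statistical analysis plan that was not available here may already include service. A reader might infer that the stratification has been deliberately ignored; the protocol does not support that, since silence is not a decision. What remains is that section 7 does state the model and its clustering level, and an analysis without service would comply with it. A stratum belongs in the model because of how allocation was done, whether or not it looks like a confounder.

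Three further inferences are tempting and should be resisted.
- **That the team-only test is anti-conservative.** The error runs the other way: simulated type I error was 2.4% to 5.0%.
- **That planned power is lost.** Team-only power in the simulation was 78% to 82% and did not fall as f rose. What is forgone is a possible gain, and at f = 0.10 or below there is none.
- **That 4.5 teams per service on average makes equal arms in every service impossible.** Five services with 3 teams and five with 6 give 45, all divisible by three. Nothing in the protocol requires such numbers, so imbalance is likely but not certain.

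It is also fair to say that the planned covariates, which include education, ethnicity and earlier measurements, may absorb part of any difference between services. That would lower the effective f.

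**Conclusion.** The point holds in a limited form. Section 3 stratifies by service and section 7 does not name service in the model. If more than roughly 10% of the between-team variance lies between services, the team-only model overstates the standard error and the test is conservative. Type I error is about 4.0% at an assumed 25% share and 2.4% at 50%, and including service adds about 3 and 9 points of power respectively. If services do not differ, including service costs about 3 points.

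These sizes rest on the assumed share, the protocol's ICC of 0.10, equal team sizes and 4 or 5 teams per service. They come from unadjusted team means for a continuous outcome. The validity of the trial is not threatened; this is a worthwhile alignment of analysis with design.

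**What to change.** State in section 7, under Intervention effect, that regional service, as the randomisation stratum, enters the intervention-effect models as a fixed effect, with team as random intercept and a small-sample degrees-of-freedom correction. Allow service as a random level instead where degrees of freedom are short or a dichotomous outcome is too sparse for about nine extra terms in the multilevel logistic model, and say in advance when that alternative applies. If a separate analysis plan already does this, section 7 should say so.

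The change is one sentence and needs no new data, because each team's service is known at randomisation. The statistical price is about nine degrees of freedom (42 to 33 at team level), or roughly 3 points of power in the case where services do not differ at all. It should be fixed before outcome data are seen.

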**TIME SCHEDULE IN MONTHS**

The schedule below is provided in months from the start of the project, which is scheduled at July 1, 2008.

0-6: Recruiting 45 YHC-centers, preparing procedures/measures/protocols, and (start of) training of YHC-professionals regarding 'BOFT+' (15 YHC-teams) and the 'Healthy toddler' (15 YHC-teams) interventions.

6-18: During a year 3.000 parents of newborns will be provided information about the study and will be asked informed consent by 60 YHC-teams (expected participation rate at least 50%).

6-19: After recruitment of 1.500 parents/newborns, baseline measurements (T0 at child age 1 month) will be performed in the 3 study arms.

6-19: In the 'BOFT+' study arm (15 YHC-teams) the 'BOFT+' intervention will be started regarding 500 parents/newborns at child age 1 month.

12-24: Measurements at child age 6 months in 1.500 parents/infants (T1).

21-33: Measurements at child age of 15 months in 1.500 parents/infants (T2).

23-37: In the 'Healthy toddler' study arm (15 YHC-teams) the first part of the 'Healthy toddler' intervention will be applied to 500 parents/toddlers at child age of circa 18 months.

29-43: In the 'Healthy toddler' study arm (15 YHC-teams) the second part of the 'Healthy toddler' intervention will be applied to 500 parents/toddlers at child age of circa 24 months.

30-42: In the 'BOFT+' study arm (15 YHC-teams) the last scheduled contact moment between YHC-team and parents regarding the 'BOFT+' interventions will take place regarding 500 parents/toddlers at child age 24 months.

42-54: Measurements at child age of 36 months in 1.500 parents/infants (T3).

6-55: Data entry, and data cleaning.

18-60: Analyses, dissemination of the results.

## **4. STUDY POPULATION**

The research team will recruit circa ten services providing Youth Health Care for preschool children, with a total of 45 YHC-teams (Consultatiebureau teams) that participate in the study. The participating research centers (Erasmus MC in Rotterdam, TNO in Leiden, TU Twente in Enschede and VUmc in Amsterdam) have excellent relations with the Youth Health Care providers in the Netherlands, within and without the context of the recently established 'Academic Workplaces for Public Health' (Academische Werkplaatsen Publieke Gezondheidszorg), and foresee no difficulties in recruiting a total of 45 YHC-teams that will participate in the study.

The study population includes parents and their babies/toddlers, eligible for the regular YHC visits from birth until elementary school age (preschool YHC; Consultatiebureau zorg), during the study, that belong to one of the participating YHC services. Parents included in the study must be able to speak Dutch; severely handicapped toddlers are excluded from participation. Representative groups of parents, including those with relatively low education and from ethnic minority groups, will be included in the study. Parents will be fully informed about the study and informed consent will be obtained prior to inclusion in the study. Parents will be informed about the study when the YHC nurse visits the young parents in the second week after birth; informed consent may be provided during the first visit at the YHC center four weeks after birth. Approval of the Medical-Ethical Committee of Erasmus MC – University Medical Center Rotterdam will be obtained.

**Intervention group (a)**

The intervention group consists of parents of preschool children that participate in the study and receive preventive Youth Health Care from one of the 15 YHC-teams that is trained to administer the 'BOFT+' intervention that is described below. The 'BOFT+' intervention consists of several elements (see below), but is administered - in principle - at all regular YHC-visits.

**Intervention group (b)**

The intervention group consists of parents of preschool children that participate in the study and receive preventive Youth Health Care from one of the 15 YHC-teams that is trained to administer the 'Healthy toddler' intervention that is described below. The 'Healthy toddler' intervention is applied twice, at child-age of circa 18 months and circa 24 months old.

